### Power analysis

We estimate that 40% of patients have focal or diffuse B-lines with an altered LUS score—unexposed/exposed ratio: 1.5—and that 30% of patients have no B-lines, but could run into MACE with a relative risk of 1.5 [30, 31]. Considering that the rate of MACE in patients undergoing hip surgery is about 30%, we calculated a relative risk of 1.5. Therefore, we estimated that we would need a sample size of 877 patients in order to obtain 80% statistical power.

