**Methods:**

LUSHIP is an Italian multicenter prospective observational study. Patients will be recruited on a nation-wide scale in the 12 participating centers. Patients aged  >  65 years undergoing spinal anesthesia for hip fracture fixation will be enrolled. A lung ultrasound score (LUS) will be generated based on the examination of six areas of each lung and ascribing to each area one of the four recognized aeration patterns—each of which is assigned a subscore of 0, 1, 2, or 3. Thus, the total score will have the potential to range from a minimum of 0 to a maximum of 36. The association between 30-day postoperative complications of cardiac and/or pulmonary origin and the overall mortality will be studied. Considering the fact that cardiac complications in patients undergoing hip surgery occur in approx. 30% of cases, to achieve 80% statistical power, we will need a sample size of 877 patients considering a relative risk of 1.5.

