### Statistical analysis

Continuous normally distributed variables will be presented as means  ±  standard deviations (SD) and compared using the Student’s *t* test. Normality will be assessed using the Shapiro–Wilk test and visual inspection of quantile–quantile plots. Non-normally distributed data will be presented as medians, 1st and 3rd quartiles, and compared using the Wilcoxon rank-sum test. Categorical data will be compared between groups using the *χ*^2^ test, or Fisher’s exact test. Possible correlations between the patient outcomes and changes in LUS score will be examined using the Spearman's rank correlation coefficient. Receiver operating characteristic (ROC) curve analysis will be used to determine optimal cut-off values of LUS score for 30-day clinical deterioration (pulmonary, major cardiovascular events) and mortality. Youden’s index calculation will define the best cut-off value. Cox proportional-hazards models for mortality or clinical deterioration as endpoints allows for the calculation of hazard ratios (HR) of baseline LUS parameters. *P *values less than 0.05 will be considered to indicate statistical significance. Statistical analysis will be performed using the R environment (R Foundation for Statistical Computing, Vienna, Austria) and the appropriate packages.

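### The stated relative risk of 1.5 and event rate of about 30% do not lead to 877 patients at 80% power; effect, rate, size and power need to be reconciled

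*Protocol article*

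**What the plan says.** The Power analysis section puts the share of patients with B-lines and an altered lung ultrasound score at 40%, which it expresses as an unexposed/exposed ratio of 1.5. It then gives a figure for the comparison group: "30% of patients have no B-lines, but could run into MACE with a relative risk of 1.5". The next sentence attaches 30% to hip surgery patients in general: "Considering that the rate of MACE in patients undergoing hip surgery is about 30%, we calculated a relative risk of 1.5". The conclusion is: "we estimated that we would need a sample size of 877 patients in order to obtain 80% statistical power".

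The Abstract (Methods) takes a cardiac complication rate of roughly 30% and repeats the same pairing: "to achieve 80% statistical power, we will need a sample size of 877 patients considering a relative risk of 1.5".

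The significance level is in the Statistical analysis section: "values less than 0.05 will be considered to indicate statistical significance". Neither the Abstract nor the Power analysis section gives a formula, the sidedness of the test, a dropout allowance or any other inflation.

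**The concern.** The article supplies nearly everything needed to recompute the sample size, and the result is far from 877. A risk of 30% against 45% in groups of this ratio needs fewer than half that number.

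These two places are where the article says what effect the study is sized to detect. A reader will take it that 877 patients give 80% power against a relative risk of 1.5. On the stated inputs the power against that effect is well above 90%, and 80% power belongs to a smaller effect. That changes how a null result should be read. It also matters because the article foresees a later randomized trial, to which the effect assumption could be carried forward.

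The 30% figure adds a second problem. It is tied first to patients without B-lines and then to all hip surgery patients, and under the stated relative risk it cannot be both.

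**Working it through.** **Inputs.** Exposed share 40% and ratio r = 1.5 unexposed per exposed, MACE about 30%, relative risk (RR) 1.5, power 80%, N = 877 (Power analysis; the Abstract repeats the rate, RR, power and N). Level 0.05 (Statistical analysis). Two-sided testing is my assumption. Then (z₀.₉₇₅ + z₀.₈₀)² = (1.960 + 0.842)² = 7.849.

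**Formula (Kelsey).** With p₀ the unexposed risk, p₁ the exposed risk, d = p₁ − p₀ and p̄ = (p₁ + r·p₀)/(1 + r):

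n₁ = 7.849 · p̄(1 − p̄)(r + 1)/(r·d²), n₀ = r·n₁.

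**Step 1: try to reproduce 877 from the stated inputs.** If 30% is the unexposed risk, p₁ = 1.5 × 0.30 = 0.45, p̄ = 0.36 and d = 0.15:

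n₁ = 7.849 × 0.36 × 0.64 × 2.5/(1.5 × 0.0225) = 133.95, n₀ = 200.93, so 134 + 201 = 335.

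The Fleiss formula gives about 336 and its continuity-corrected form about 363. The other two readings of the 30% follow in the same way. If 30% is overall, p₀ = 0.30/(0.6 + 0.4 × 1.5) = 0.25. If 30% is the exposed risk, p₀ = 0.30/1.5 = 0.20.

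| Reading of the 30% | p₀ vs p₁ | N, Kelsey to continuity-corrected |
|---|---|---|
| Unexposed | 30% vs 45% | 335–363 |
| Overall | 25% vs 37.5% | 440–476 |
| Exposed | 20% vs 30% | 597–645 |

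Rounding each group up moves these totals by one or two patients. One-sided testing widens the gap: 265–293 for the first reading. No reading gives 877.

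**Step 2: power at 877 for RR 1.5.** Take 351 exposed and 526 unexposed, with z = (d − 1.96·SE₀)/SE₁, where SE₀ is the pooled and SE₁ the unpooled standard error.

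- Unexposed 30%: (0.150 − 1.96 × 0.0331)/0.0332 = 2.56, power 99.5%.
- Overall 30%: (0.125 − 1.96 × 0.0316)/0.0320 = 1.97, power 97.6%.
- Exposed 30%: (0.100 − 1.96 × 0.0294)/0.0300 = 1.41, power 92.0%.

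With RR 1.5, 877 patients would give 80% power only at an unexposed risk of about 15%, half the stated figure.

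**Step 3: what does give 877.** Read 1.5 as an odds ratio with 30% in the unexposed and change nothing else. The exposed odds are 1.5 × 0.30/0.70 = 0.643, so p₁ = 0.643/1.643 = 0.391 and RR = 0.391/0.30 = 1.30. With p̄ = 0.3365 and d = 0.0913, n₁ = 350.36 and n₀ = 525.54. Rounded up, 351 + 526 = 877. Power at that size is 79.9%. Fleiss gives 882–883, and 927 with continuity correction.

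**Step 4: can 30% be both rates?** With 40% exposed and RR 1.5, 30% in the unexposed implies 0.6 × 30% + 0.4 × 45% = 36% overall. It cannot also be 30%.

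**The case against.** **The odds ratio is nowhere in the article.** A reader might infer that 877 was calculated from an odds ratio. The documents do not support stating that as fact: no odds ratio, formula or sidedness is given, and the exact match needs the Kelsey formula with each group rounded up. It remains a strong inference, because it changes a single input and adds none. Other combinations that come close to 877 need something the article does not state or contradicts, such as a level of 0.01, 90% power, 30% dropout or equal groups. The contradiction in steps 1 and 2 does not depend on this explanation.

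**The sentence on the 30% is garbled.** Reading it as the risk in patients without B-lines is interpretation. This stands, and it is why three readings are shown. Taken literally, as the share of patients without B-lines, 30% would conflict with the 60% that a 40% exposed share leaves. The 36% versus 30% clash is thus best put as an ambiguity to be resolved. The statement that the relative risk was calculated may simply mean that it was assumed from the cited sources, so nothing is built on that word.

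**Nothing is underpowered.** A reader might infer a shortfall, since an odds ratio of 1.5 combined with a 30% overall rate would have 77.5% power at 877. The article never states that pairing. For the relative risk it does state, 877 is more than enough on every reading. The study is observational and does not alter patient management, so this is a reporting correction. It still corrects a headline figure that does not follow from its own inputs.

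**Conclusion.** The point holds as an internal contradiction. A relative risk of 1.5, MACE of about 30%, 877 patients and 80% power do not describe one design. The required number is 335–363, 440–476 or 597–645, and power at 877 is 99.5%, 97.6% or 92.0%, according to whether the 30% belongs to the unexposed, to everyone or to the exposed. This rests on two-sided testing at 0.05 and a comparison of two proportions in the stated ratio.

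An odds ratio of 1.5 with 30% in the unexposed is the likely but unstated source of 877. If 30% is the unexposed risk, the effect that 877 patients detect with 80% power is a relative risk of about 1.30. The group to which the 30% applies is unclear and has to be fixed before any restated power figure is final.

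**What to change.** Keep 877 and leave enrolment unchanged. State once which group the 30% describes, state that the test is two-sided if it is, and make the Power analysis section and the Abstract agree. The wording depends on what the sponsor confirms:

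- **If an odds ratio was used with 30% in patients without B-lines:** *877 patients give 80% power for an odds ratio of 1.5 (39.1% versus 30%, relative risk 1.30).*
- **If a relative risk of 1.5 was intended:** restate the power at 877 as about 99% (30% in the unexposed) or about 98% (30% overall), and give the smallest relative risk detectable with 80% power, which is about 1.30 with 30% in the unexposed.

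The effect should not be redefined as an odds ratio merely because it fits the number.

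Describe the unexposed group as the Power analysis section does, as patients without B-lines, and not as patients with a lung ultrasound score of 0. Under the Protocol for lung ultrasound section, an area scores 0 with fewer than two B-lines, so the two groups are not the same.

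The cost is a few sentences in two places. Design, data collection and recruitment are not affected.

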## Discussion

Patients with hip fracture encounter a significant risk of morbidity and mortality in the postoperative period [5, 30, 31]. The principal causes are cardiac-decompensated heart failure and myocardial infarction being the main diseases in this setting since the population is usually old (90% are aged  >  65 years) with the presence of underlying coronary artery disease [32, 33]. The number of patients undergoing this type of surgery is expected to increase over the coming years [31]. Thus, an extraordinary effort should be made to assess these patients in the preoperative setting. The ESA/ESC and ACC/ASA guidelines have attempted to provide the means to predict and quantify the risk of perioperative morbidity and mortality due to cardiac origin through a number of scoring systems [3, 4, 12]. However, the RCRI has shown only moderately accuracy in predicting the overall patient mortality risk as to the other scores [11]. That said, the evaluation of physical status with METS endorsed by ESA/ESC and ACC/ASA, is currently being assessed as part of a large observational study to ascertain its utility, both in self-reporting as well as METS testing [14]. The results of the “MET-repair” study are expected to be presented soon. The Canadian guidelines on perioperative evaluation have assigned a central role to BNP and Pro-BNP in their algorithm; however, while natriuretic peptides have been shown to have high negative predictive value, they do not have high positive predictive value [15]. Indeed, one study reported that clinicians perceive BNP to increase postoperative risk in only 66% of the patients [34].

More and more anesthesiologists are turning to LU [35]. Some studies reveal LU to have higher diagnostic accuracy than chest X-rays in the perioperative setting for the direct assessment of the most frequent lung diseases, such as pleural effusion, consolidation, and interstitial syndrome [20, 36]. Another recent study in vascular surgery patients (the LUPPO study) indicated that LU could help evaluate “indirect” cardiac status at the bedside [19]. This is because B-lines tightly correlate with interstitial lung syndrome of cardiac origin [37]. On the contrary, the absence of multiple B-lines excludes pulmonary edema with a high negative predictive value [24, 38]. Furthermore, an expert consensus document reporting a checklist for the quantification of pulmonary congestion by LU in heart failure reports that LU can provide useful information [24]. Considering the above, we designed this multicenter observational study to assess the utility of LU in the management of frail elderly patients undergoing hip fracture repair.

Our study protocol has some limitations: first of all, the different participating centers may have different levels of experience in LU use and may operate different ultrasound machines for LU evaluation; second, distinct perioperative clinical management in different centers could influence patient clinical course and the incidence of complications. However, if we demonstrate LU to have the ability to predict postoperative cardiac and pulmonary complications in hip fracture patients, our observational study will help pave the way to the generation of future hypotheses and the design of further randomized clinical trials directed at improving patient outcome. To say that we acknowledge as a study limitation that patients with known acute heart failure or MACE at “priori” were excluded to have a pure vision about LU prediction.

## Conclusions

The study is currently in the enrollment phase. Due to the COVID-19 outbreak, we experienced a reduction in enrollment rates in March, April and May 2020. However, the study is expected to reach the required sample size by the end of 2021.

## Data Availability

Not applicable.

## Abbreviations

ASA-PS: American Society of Anesthesiologists Physical Status
ESC: European Society of Cardiology
ESA: European Society of Anesthesiology
RCRI: Revised Cardiac Risk Index
NSQIP-MICA: National Surgical Quality Improvement Program Myocardial Infarction and Cardiac arrest
ACC: American College of Cardiology
AHA: American Heart Association
METS: Metabolic equivalents
BNP: Brain natriuretic peptide
NT-pro-BNP: Pro-natriuretic peptide
NPV: Negative predictive value
ACP: American College of Physicians
COPD: Chronic obstructive pulmonary disease
CEUR-FVG: Ethic Committed of Friuli Venezia Giulia
MACE: Major advance cardiac events
ESICM: European Society of Intensive Care Medicine
GDPR: General data protection regulation
CRF: Case report form
PI: Principal investigator
STARD: Standards for the Reporting of Diagnostic Accuracy Studies
POCUS: Point-of-care ultrasound statement
SD: Standard deviation
ROC: Receiver operating characteristic
HR: Hazard ratios
